### Sample size calculation

The intervention and control groups are of equal size, and two-tailed hypothesis testing is assumed. The sample size is calculated using the Stata software CRCT sample size function. By setting the power = 90%, α = 0.05, and desired confidence level = 95%, the number of clusters per arm is 66, and the sample size of each arm is 1,056. Assuming a retention rate of 80% during follow-up, 20 participants are needed for each cluster, totaling 3,960 participants for the entire study.

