### Outcomes measures

#### Primary outcomes

One of the study’s primary outcomes is HIV-related knowledge improvement, which is obtained by calculating weighted scores for the indicators in the HIV Related Knowledge Scale to represent the participants’ and their family members’ level of knowledge measured by the baseline and follow-up questionnaires. The research team will compare the control group and the two intervention groups to investigate whether the groups receiving the mobile-based HIV-related health education develop a deeper understanding of HIV-related knowledge than the control group which did not receive the intervention. For the second primary outcome, the research team will compare “Intervention A” and “Intervention B” to determine what type of financial reward, standardized compensation or participant performance-based compensation, is more effective at incentivizing village doctors to deliver and promote the content of the intervention. The difference between the cost-effectiveness and the participants’ HIV-related knowledge improvement of the two groups will be used to evaluate which intervention yields a more effective outcome.

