### Data analysis

The research team will use descriptive analysis to summarize the socio-demographic characteristics of the general participants and various subgroups, HIV related knowledge, physical and mental health status, attitudes toward HIV, and lifestyle habits such as condom and drug use. The team will compare the baseline data between the intervention groups and the control group to measure the equivalence of the characteristics at baseline by using a t-test, and chi-squared-test and calculating the standard difference.

To investigate the effect of the mobile-based HIV-related message intervention, the team will use a t-test and chi-squared test to compare the significance of the intervention-related difference between groups at 6-, 12-, and 18-months. Since the outcomes are measured using numerical values (e.g., HIV-related knowledge, scores from 1 to 100), binary values (0,1) and categorical types (e.g., level of engagement, ranges from 1 to 6), different regression models (ordinary least squares, generalized linear mixed models) will be used for analysis according to the unique circumstances. Finally, sub-analysis will be conducted for the different age, gender, and education groups to explore the evidence of the effects related to various characteristics.

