The proposed study has several strengths. First, is study establishes a reproducible method, using mobile phones to carry out the intervention in poor areas where on-site intervention is extremely difficult, aggravated by factors such as the low education level of the local population, scattered geographical locations, and inconvenient transportation. Second, the study has a large sample size of more than 4000 participants in more than 200 villages, enabling the collection of a large data set for analysis and interpretation. Third, the study evaluates the secondary transmission of knowledge, in which the research team examines whether HIV-related knowledge will be transmitted to other members of the family by the participants, and tests the effectiveness of the transmission. Fourth, the study is the first to examine what type of monetary reward is more effective at motivating village doctors in rural China to engage in their role and responsibilities during the intervention. This measure explores the possibility of increasing utilization of village doctors in the future to carry out various disease and behavioral interventions in other places. Lastly, the study design has high reproducibility and generalizability, making it easy to replicate in other areas of China and other middle / and low-income countries.

One limitation of this study is worth noting. Although the participants are required not to join other HIV-related experimental interventions, it is impossible to prevent them from communicating with participants in other studies. Therefore, some may be subject to small-scale knowledge transmission from other interventions, which might introduce bias. For this part of the population, the research team will take measures in the data analysis process to reduce the impact of the bias.

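### Two primary comparisons are tested at 6, 12 and 18 months with no primary visit or lead contrast, and the 90% power is tied to no named comparison or difference

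*Protocol article*

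**What the plan says.** **Primary comparisons.** Under Primary outcomes, the first question is knowledge: "The research team will compare the control group and the two intervention groups to investigate whether the groups receiving" the messages understand more than control. Whether A and B are pooled or taken separately against control is not said. The second question is A versus B, judged on knowledge improvement and cost-effectiveness.

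**Tests.** Under Data analysis, t-tests and chi-squared tests will "compare the significance of the intervention-related difference between groups at 6-, 12-, and 18-months". Regression models are also mentioned. No visit is called primary, no contrast comes first, and no significance level appears in that section.

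**Sample size.** The paragraph opens with "The intervention and control groups are of equal size, and two-tailed hypothesis testing is assumed". It sets "By setting the power = 90%, α = 0.05" and concludes that "the number of clusters per arm is 66, and the sample size of each arm is 1,056". It then adds: "Assuming a retention rate of 80% during follow-up, 20 participants are needed for each cluster, totaling 3,960 participants for the entire study". It gives no target difference, standard deviation or intracluster correlation (ICC).

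**Totals.** The Abstract, Study design overview and Study setting sections give 200 villages. The Discussion says that "the study has a large sample size of more than 4000 participants in more than 200 villages".

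**The concern.** A reader cannot tell which result decides the trial. Three visits and at least two primary-level contrasts have the same standing, so a success claim could rest on whichever one reaches significance. Naming the visit or contrast after outcome data are seen would not be credible.

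The power statement raises a related problem. A and B deliver the same messages and identical videos, and the planned difference is how the village doctor is paid. If A improves knowledge over control, B's advantage over A is smaller than B's advantage over control. The article makes A versus B a primary question but gives no difference that it was sized to detect. A null result could then be read as showing that the type of pay does not matter, with nothing in the plan to say how large a difference could have been missed.

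**Working it through.** **1. The plan's own figures.**
- 1,056 / 66 = 16 analysed per village, and 16 / 0.80 = 20 recruited.
- 66 × 20 × 3 = 3,960 participants, and 66 × 3 = 198 villages.
- The arithmetic is consistent. The 66 villages per arm cannot be re-derived, because no difference, SD or ICC is given.

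**2. False-positive chance at one visit, each test at two-sided 5%.**
- Pooled A+B versus control and A versus B are uncorrelated when the arms are equal. The chance of at least one false positive is 1 − 0.95² = 9.75%, about 10%.
- Testing all three arm pairs instead gives 12.2% by simulation (400,000 draws, equal arms).

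**3. The same over three visits.** The between-visit correlation of the arm means is an assumption. Simulation (400,000 draws) gives the chance for one contrast over three visits, p. Because the two contrasts are uncorrelated across visits too, the chance for both is 1 − (1 − p)².

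| Correlation | One contrast (p) | Two contrasts | All three pairs |
|---|---|---|---|
| 0.3 | 13.6% | 25.4% | 30.9% |
| 0.5 | 12.5% | 23.5% | 28.6% |
| 0.7 | 10.9% | 20.6% | 24.9% |

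For the three-pair reading, widening the correlation to 0 and 0.9 gives 32% and 19%. These figures count knowledge only, presume correct cluster standard errors, and leave out cost-effectiveness.

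**4. What 90% power implies for A versus B.** At two-sided 0.05, 90% power means that the design difference is 1.960 + 1.2816 = 3.2415 standard errors. With equal arms the standard error is the same for any pair. If the true A-versus-B difference is a fraction f of the design difference, power = Φ(3.2415f − 1.960):
- f = 1: Φ(1.282) = 90%
- f = 2/3: Φ(0.201) = 58%
- f = 1/2: Φ(−0.339) = 37%; restoring 90% would need 66 / 0.5² = 264 villages per arm

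The fractions are illustrations, not figures from the article.

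**5. What the design difference might be.** With design effect 1 + 15 × ICC and 1,056 analysed per arm, the difference detectable with 90% power is 3.2415 × √(2 × design effect / 1,056). For an assumed ICC of 0.01 this is 3.2415 × √(2 × 1.15 / 1,056) = 0.15 SD. For an assumed ICC of 0.20 it is 3.2415 × √(2 × 4 / 1,056) = 0.28 SD.

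**6. Totals.** The sample size paragraph gives 198 villages and 3,960 people. Elsewhere 200 villages × 20 = 4,000 people. The Discussion claims more than both.

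**The case against.** The strongest reply is that this is a journal article. Primary timepoint, order of testing and multiplicity handling are often set out in a full protocol or SAP that is not shown, so their absence here proves nothing about the trial. This stands in part, since an adjustment may exist elsewhere. But the article does state a testing rule, and that rule gives three visits equal standing. The contrast and difference also belong beside the 90%, because without them that figure has no meaning.

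A reader might infer several stronger claims that the text does not support:

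- **Every test is run at 5%.** The 0.05 appears only in the sample size paragraph, so the error rates above are conditional on that reading.
- **There are nine primary tests.** Three pairs at three visits is one reading. The Primary outcomes text can equally mean pooled intervention versus control, then A versus B. The 25-31% range belongs to the wider reading only.
- **The 90% covers one arm against control and excludes A versus B.** The paragraph speaks of intervention and control groups but names no contrast. With equal arms, A versus B has the same power for the same difference.
- **A versus B is bound to be underpowered.** Its difference may be smaller than B versus control and still match the design difference, for example if A gains one design difference and B gains two.
- **200 villages cannot be allocated.** An exact three-way split is impossible, but 67/67/66 is ordinary practice, and 200 can be seen as 198 rounded up.

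A fixed order starting with the pooled test is also one acceptable scheme among several. Holm or a split alpha would serve.

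**Conclusion.** The point holds at moderate severity. The article sets two primary comparisons and tests at three visits without saying which visit or contrast leads. If each test is taken at 5% and visit correlations are 0.3 to 0.7, the false-positive chance is about 21-25% for two contrasts, or 25-31% if all three pairs are tested. Confining the two contrasts to one visit brings it to about 10%, and a fixed order brings it to 5%.

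On power, the supported conclusion is that no comparison or difference is attached to the 90%, and that A versus B is not addressed separately. The 58% and 37% figures show how sensitive its power is; they do not predict it. The conflict in totals is real but minor.

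**What to change.** In Data analysis, name 18 months, the end of the intervention, as the primary visit and make 6 and 12 months secondary. At 18 months, test the two primary comparisons in fixed order at two-sided 0.05: A+B pooled versus control on knowledge, then A versus B. An equivalent error-controlling rule would also do.

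In Sample size calculation, state which comparison and what difference the 90% refers to, and give the detectable difference for A versus B. Use one total throughout: 198 villages and 3,960 participants, or 200 villages as 67/67/66 and 4,000 participants.

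The cost is wording, with no extra participants and no split of alpha. The downside of the fixed order is that A versus B is confirmatory only if the first test succeeds. If the sponsor will not accept that, Bonferroni at 0.025 for each comparison avoids the dependence. Power at the design difference would then fall from 90% to 84%, or about 78 villages per arm would be needed to keep 90%. Either choice should be fixed before outcome data are seen.

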## Discussion

Our goal is to establish a scalable, effective, acceptable, and convenient mobile-based information intervention model to improve HIV-related knowledge, attitudes, practices, and health outcomes in poverty-stricken areas in China and measure the impact of incentive policies on the work of village doctors. To our knowledge, this is the first study to evaluate the effectiveness of dissemination of primary and secondary knowledge through a mobile-based HIV prevention intervention on participants and their family members residing in poor areas, cooperating with the local Health Commission and incentivizing village doctors to deliver HIV-related informational messages, including contents on basic HIV facts, key populations, transmission, symptoms, testing, treatment, related laws, and harmful consequences. In this scenario, a mobile-based online intervention involving WeChat and the Chinese Version TikTok has the potential to disseminate HIV-related knowledge effectively, reduce risky behaviors, increase self-protection awareness, and control HIV infection. The widespread use of mobile phones and these applications have enabled a new and effective way to deliver messages even in the most impoverished areas, making it possible to deliver the intervention comprised of group information dissemination and individualized communication [40].

The proposed study has several strengths. First, is study establishes a reproducible method, using mobile phones to carry out the intervention in poor areas where on-site intervention is extremely difficult, aggravated by factors such as the low education level of the local population, scattered geographical locations, and inconvenient transportation. Second, the study has a large sample size of more than 4000 participants in more than 200 villages, enabling the collection of a large data set for analysis and interpretation. Third, the study evaluates the secondary transmission of knowledge, in which the research team examines whether HIV-related knowledge will be transmitted to other members of the family by the participants, and tests the effectiveness of the transmission. Fourth, the study is the first to examine what type of monetary reward is more effective at motivating village doctors in rural China to engage in their role and responsibilities during the intervention. This measure explores the possibility of increasing utilization of village doctors in the future to carry out various disease and behavioral interventions in other places. Lastly, the study design has high reproducibility and generalizability, making it easy to replicate in other areas of China and other middle / and low-income countries.

One limitation of this study is worth noting. Although the participants are required not to join other HIV-related experimental interventions, it is impossible to prevent them from communicating with participants in other studies. Therefore, some may be subject to small-scale knowledge transmission from other interventions, which might introduce bias. For this part of the population, the research team will take measures in the data analysis process to reduce the impact of the bias.

## Data Availability

Not applicable.

## Abbreviations

AIDS: acquired immuno deficiency syndrome
CNY: Chinese yuan
HIV: human immunodeficiency virus
IDU: Injection drug user
MSM: Men who have sex with men
